**16. DATA COLLECTION AND INTERVENTION**

Both intervention and the control groups will continue with their usual care including all medical visits, tests, and diabetes support programmes. In addition, the intervention group will receive SMS at an agreed time and days of the week tailored according to their needs, goals and their care plan. Participants will as well receive motivational and support messages and they can opt to receiving additional messages on topics such as lifestyle intervention; diets, physical activity and smoking cessation. Where appropriate to their care, patients will also receive reminders to check their blood glucose levels, insulin or drug use. Contacts to be reached in case of any query will be provided at the end of the message. Call records will be kept.

Data will be collected at baseline, and six months after the intervention. Baseline data will include demographic characteristics including duration of diabetes, behavioural factors (smoking, physical inactivity, alcohol use), anthropometric measurements (weight, height, waist and hip circumferences) and biochemical measurements (random blood sugar). At baseline, the demographic characteristics, particularly, age, and duration of diabetes as well as mean blood sugar will be balanced between both arms.

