**The specific objectives of the study are:**

- Determine the efficacy and acceptability of mobile phone SMS in promoting glycaemic control among individuals living with diabetes in the Eastern Cape Province.
- Determine the efficacy and acceptability of mobile phone SMS in promoting adherence to medication, physical activity and recommended diets among individuals living with diabetes in the Eastern Cape Province.
- Determine the effectiveness of the use of mobile phone SMS as a clinic appointment reminder or awareness promoter about diabetes and its complications.
- Determine the efficacy of the use of mobile phone SMS in improving diabetes knowledge among individuals living with diabetes in the Eastern Cape Province.
- Determine the healthcare providers’ perspective on the use of mHealth technology in diabetes control in the Eastern Cape Province; and
- Determine the efficacy of text messaging in improving other secondary clinical outcomes (body weight, blood pressure and body mass index).

1. **RESEARCH QUESTIONS**

- Would the use of mobile phone SMS be effective in promoting glycaemic control among individuals living with diabetes?
- Would the use of mobile phone SMS be effective in promoting adherence to medication, physical activity and dietary recommendations among individuals living with diabetes?
- Would the use of mobile phone SMS be effective in promoting diabetes knowledge among individuals living with diabetes?
- How effective is the mobile phone SMS as a clinic appointment reminder and awareness promoter on diabetes and its complications?
- What are the likely barriers to the use of SMS in conveying health information to persons living with diabetes in the Eastern Cape Province?
- How do the healthcare providers perceive mHealth technology as a feasible option in the control of diabetes?

1. **SIGNIFICANCE OF THE STUDY**

Poor adherence to anti-diabetic therapy has been identified as a threat to effective glycaemic control as well as prevention of complications among individuals living with diabetes. Since diabetes is chronic in nature, patient’s involvement in their care as well as improvement in their self-care management behaviour will go a long way in improving their quality of life.

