**11. RESEARCH DESIGN**

This study will adopt a quantitative, descriptive, interventional approach to determine the efficacy, acceptability and feasibility of the mHealth technology in promoting adherence to anti-diabetic therapy and glycaemic control among diabetic patients in the Eastern Cape Province. This will be an interventional study, utilising a randomised controlled trial to compare six months standard care with a mobile phone-based SMS intervention among diabetic patients receiving treatment.

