**18. SECONDARY OUTCOME MEASURES**

The secondary outcome measures will be assessed at three and six months namely;

- Knowledge on diabetes which will be obtained with the validated Michigan Diabetes Knowledge Test Questionnaire-2 (Fitzgerard et al., 2016).
- Medication adherence, using a pre-validated self-developed medication adherence questionnaire.
- Clinic attendance, using clinic registers.
- Quality of life, using the EQ-5D self-perceived quality of life questionnaire (EURO-QOL Group, 2009).
- Barriers to SMS intervention and the healthcare providers’ perception about SMS use using a self-designed questionnaire.
- Clinical (hypertension, overweight/obesity) and behavioural outcomes (Smoking, alcohol use, and physical activity) will be measured using the WHO modified STEPwise approach.
- Factors affecting adherence to diabetes therapy using a self-designed questionnaire

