**21. DATA ANALYSIS**

All treatment evaluations will be performed on the principle of intention-to treat (ITT), using the observed data collected from all randomised participants. Comparison of the baseline and the subsequent readings of the HbA1c will be determined. Primary outcome will be analysed with the chi-square. Descriptive statistics will be used to summarise the demographic and baseline characteristics. Continuous variables will be summarised as numbers of observed values, means, standard deviation, median, minimum and maximum. Categorical variables will be described as frequency and percentage. Linear regression model will be used to test the effect of intervention on the primary outcome between the two groups. All statistical tests will be two-sided at 5% significance level. The Statistical Package for Social Sciences (SPSS) version 22 will be used for all statistical analysis.

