**24. TIME FRAME**

The proposed timeline for the study is illustrated in Table 1.

**Table 1**: Timeline for the research project

|  | Months | | | | | | | | | | | | | | | | | |  |
| --- | --- | --- | --- | --- | --- | --- | --- | --- | --- | --- | --- | --- | --- | --- | --- | --- | --- | --- | --- |
| Activity | April 2017 | May, 2017 | June, 2017 | July, 2017 | Aug 2017 | Sept 2017 | Oct. 2017 | Nov. 2017 | Dec. 2017 | Jan, 2018 | Feb, 2018 | Mar, 2018 | April 2018 | May 2018 | June, 2018 | July 2018 | Aug., 2018 | Sept..2018 | May 2019 |
| Writing of research proposal |  |  |  |  |  |  |  |  |  |  |  |  |  |  |  |  |  |  |  |
| Literature review |  |  |  |  |  |  |  |  |  |  |  |  |  |  |  |  |  |  |  |
| Presentation of proposal to the faculty |  |  |  |  |  |  |  |  |  |  |  |  |  |  |  |  |  |  |  |
| Registration with senate higher degree committee |  |  |  |  |  |  |  |  |  |  |  |  |  |  |  |  |  |  |  |
| Registration with the provincial Department of Health |  |  |  |  |  |  |  |  |  |  |  |  |  |  |  |  |  |  |  |
| Registration with the Districts Department of Health |  |  |  |  |  |  |  |  |  |  |  |  |  |  |  |  |  |  |  |
| Formulation of the SMS by the team |  |  |  |  |  |  |  |  |  |  |  |  |  |  |  |  |  |  |  |
| Training of research assistant |  |  |  |  |  |  |  |  |  |  |  |  |  |  |  |  |  |  |  |
| Baseline Data collection |  |  |  |  |  |  |  |  |  |  |  |  |  |  |  |  |  |  |  |
| Data capturing |  |  |  |  |  |  |  |  |  |  |  |  |  |  |  |  |  |  |  |
| Collection of data after 3 months |  |  |  |  |  |  |  |  |  |  |  |  |  |  |  |  |  |  |  |
| Literature review continues |  |  |  |  |  |  |  |  |  |  |  |  |  |  |  |  |  |  |  |
| Collection of data after 6 months |  |  |  |  |  |  |  |  |  |  |  |  |  |  |  |  |  |  |  |
| Data capturing |  |  |  |  |  |  |  |  |  |  |  |  |  |  |  |  |  |  |  |
| Data Analysis |  |  |  |  |  |  |  |  |  |  |  |  |  |  |  |  |  |  |  |
| Compilation of reports |  |  |  |  |  |  |  |  |  |  |  |  |  |  |  |  |  |  |  |
| Submission for examination |  |  |  |  |  |  |  |  |  |  |  |  |  |  |  |  |  |  |  |
| Final corrections |  |  |  |  |  |  |  |  |  |  |  |  |  |  |  |  |  |  |  |
| Graduation |  |  |  |  |  |  |  |  |  |  |  |  |  |  |  |  |  |  |  |

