**25. RESEARCH BUDGET**

| **Activity** | **Estimated Cost** |
| --- | --- |
| Printing of questionnaires for the baseline and final data collection | R10000 |
| Printing of informed consent | R8000 |
| Employment of Research Assistants for data collection at baseline and at 6 months | R40,000 |
| Procurement of instruments (Laptop, data storage device, Point of care device for sugar, test-stripes for sugar) Blood pressure apparatus, height and weight scale) | R30000 |
| Employment of Nurses involved in dispatching SMS and follow-up for the period of 6 months | R30,000 |
| Procurement of recharge cards for disseminating SMS for the period of study | R40000 |
| Data Capturing at baseline, 3 months and 6 months | R20,000 |
| Logistics(accommodation during data collection, transport, miscellaneous) | R22,000 |
| Data Analysis | R15,000 |
| Language Editing | R10000 |
| Printing and binding of dissertation | R7,000 |
| Presentation of results at Conferences | R15,000 |
| Printing and binding of dissertation | R3000 |
| Total | R250,000 |

26. **REFERENCES**

Adisa, R. & Fakeye, T.O. (2014). Treatment non-adherence among patients with poorly controlled type 2 diabetes in ambulatory care settings in southwestern Nigeria. *African Health Sciences*, 14(1):1–10.

Aikens, J.E. & Piette, J.D. (2012). Longitudinal association between medication adherence and glycaemic control in type 2 diabetes. *Diabetic Medicine*, 30: 338–345.

American Diabetes Association (2011). Standards of Medical Care in Diabetes-2011. *Diabetes Care*, 34(1):S11–S61.

American Diabetes Association (2015). *Definition of Diabetes. Definition of diagnosis*. Available at: http://www.diabetes.org/diabetes-basics/diagnosis/ [Accessed June 22, 2015].

American Diabetes Association (2003). Treatment of hypertension in adults with diabetes. *Diabetes Care*, 26(Supplement 1): 80–82.

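### Section 16 omits the three-month collection required elsewhere and misplaces the six-month visit; separately, the observed-data analysis of the primary outcome is complete-case despite its ITT label

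*Protocol*

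**What the plan says.** Section 16 gives the collection schedule in one sentence: "Data will be collected at baseline, and six months after the intervention". It mentions no collection in between.

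Other parts of the protocol describe a different schedule:

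- Section 11 sets the length of the comparison: "utilising a randomised controlled trial to compare six months standard care with a mobile phone-based SMS intervention".
- Section 17 defines the primary outcome as the change in random blood glucose between baseline and month six.
- Section 18 says "The secondary outcome measures will be assessed at three and six months namely". Its list covers knowledge, adherence, clinic attendance, quality of life, and clinical and behavioural measures. It does not include glucose.
- Section 24, Table 1, has a row labelled "Collection of data after 3 months" and another for six months.
- Section 25 has two lines that disagree. One is "Data Capturing at baseline, 3 months and 6 months"; the other is "Employment of Research Assistants for data collection at baseline and at 6 months".

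On analysis, Section 21 claims intention-to-treat, "using the observed data collected from all randomised participants", and names a linear regression for the effect on the primary outcome. Section 14 allows for 20% loss to follow-up.

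**The concern.** There are two separate matters.

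The first is the schedule. Field staff would work from Section 16, which tells them to collect twice. The budget for their time says the same. Section 18 and the timeline need a third round, and the data-capture line pays to enter its results. If Section 16 is followed, the three-month questionnaires and measurements are never taken and cannot be recovered later. Clinic attendance is the exception, because it is read from clinic registers. In addition, the phrase placing follow-up six months after a six-month programme does not match an outcome that runs from baseline to month six. No section says from which date the months are counted. Section 15 randomises after the baseline data and then contacts the intervention arm about language and timing, so baseline, randomisation and first message can fall on different days.

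The second is the analysis set. With one follow-up glucose, a participant without a six-month value has no change score and drops out of a regression on observed data. The label says intention-to-treat, but the set analysed is the completers. What is at stake is the description of the result, and its validity if loss is related to change in glucose.

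**Working it through.** **Schedule, side by side**

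| Place | Baseline | Month 3 | Month 6 |
|---|---|---|---|
| Section 16 | yes | no | worded as six months after the intervention |
| Section 17 (primary) | yes | not mentioned | yes, counted from baseline |
| Section 18 (secondary) | not mentioned | yes | yes |
| Section 24, Table 1 row labels | yes | yes | yes |
| Section 25, data capture | yes | yes | yes |
| Section 25, research assistants | yes | no | yes |

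Three places include month three (Section 18, Table 1 and the data-capture line). Two give full schedules that leave it out (Section 16 and the research-assistant line). Only the row labels of Table 1 were used, since the month cells carry no marks in the text at hand.

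**Room in the budget**

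The Section 25 lines, in thousands of rand: 10 + 8 + 40 + 30 + 30 + 40 + 20 + 22 + 15 + 10 + 7 + 15 + 3 = 250. This equals the stated total, and there is no contingency line. Research assistants cost R40,000 for two rounds. If a third round costs the same as each of those (an assumption), it is R40,000 / 2 = R20,000, or 20 / 250 = 8% of the budget.

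**The plan's own sample size (Section 14)**

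Inputs: difference 0.5 and SD 1 (HbA1c percentage points), two-sided 5%, 90 per arm, 20% loss, 108 per arm.

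- Power = Φ(0.5 / √(2/90) − 1.96) = Φ(3.354 − 1.960) = 0.918. The stated power of over 90% is reproduced.
- 90 × 1.2 = 108, which is the stated figure. Dividing instead, 90 / 0.8 = 112.5, would give 113.

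**What the observed-data rule leaves out**

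- Enrolled: 2 × 108 = 216.
- Lost at 20%: 216 × 0.20 = 43.2, about 43.
- Analysed per arm: 108 × 0.80 = 86.4, about 86.
- Power on the Section 14 assumptions: Φ(0.5 / √(2/86.4) − 1.96) = 0.908, about 91%.

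Other loss rates (assumed, to show the range):

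| Loss | Left out of 216 | Power |
|---|---|---|
| 10% | about 22 | 0.936 |
| 20% (planned) | about 43 | 0.908 |
| 30% | about 65 | 0.867 |
| 40% | about 86 | 0.812 |

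These powers are on the HbA1c scale. The protocol gives no effect or SD for random glucose, so they do not carry over to the primary outcome.

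**When bias would arise**

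Let g be the mean change in those lost minus the mean change in those seen. If g is the same in both arms, the bias in the unadjusted SMS-minus-control difference in change is (loss in control − loss in SMS) × g. It is zero if the losses are equal or if g is zero. Section 14 gives only an overall loss of 20%. The protocol gives neither the split by arm nor g, so no value can be put in.

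**The case against.** The strongest reply is that the primary time point is clear. Section 17 defines it as month six from baseline, Section 11 compares six months of care, and Section 10.2 assesses outcomes when the intervention ends. Table 1 has no collection later than the six-month row, and Section 25 pays for collection at six months and for six months of message dispatch. A reader might infer from Section 16 that follow-up falls at about month 12 and that the primary endpoint is in doubt. That rests on a literal reading of one loose phrase, and every other section points the other way. This part of the reply stands: the phrase needs correcting, but the endpoint is not in question.

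A reader might also infer a bias of definite size against SMS, because one objective is to "Determine the effectiveness of the use of mobile phone SMS as a clinic appointment reminder" and attendance at the outcome visit could then differ by arm. The documents do not support this. The objective concerns clinic appointments, and nothing says that study visits are called through the messages. The primary outcome is a change, so a higher glucose level in non-attenders that was already present at baseline would cancel. Attendance by arm is not given.

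It can also be said that missing-data handling is commonly left to a statistical analysis plan, and that a regression on observed data with baseline adjustment is valid when missingness depends only on arm and the modelled baseline variables. Both statements are fair. However, Section 21 itself fixes observed data under an intention-to-treat label, and the regression it names is not said to adjust for baseline glucose.

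Finally, the absence of a three-month glucose is inferred from Sections 17 and 18. Table 1 does not say what is measured at month three, and Section 21 refers to later HbA1c readings. That caveat stands.

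None of this removes the mismatch over month three.

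**Conclusion.** The schedule contradiction holds on the protocol's own words. Section 16 and the research-assistant line leave out a three-month round that Section 18, the timeline and the data-capture line require. If Section 16 is followed, one of the two follow-up rounds of secondary data is lost, apart from clinic attendance. The six-month visit is badly worded, but its intended place is clear from the other sections.

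The analysis point holds in a limited form. Given a single follow-up glucose, Section 21 describes a complete-case analysis that leaves out about 43 of 216 at the planned loss. Loss of power is not the harm: it stays near 91% on the stated HbA1c assumptions. Bias is possible if loss differs by arm and is related to change in glucose, but the documents neither show this nor allow it to be sized.

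**What to change.** **Schedule.** Restate Section 16 as baseline, three months and six months, counted from randomisation, with six months the time point for the primary comparison. Add month three to the research-assistant line in Section 25. The wording costs nothing. The third collection round does cost money (about R20,000 under the equal-cost assumption above), and the budget has no slack, so funds must be moved or added.

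**Analysis.** In Section 21, describe the primary analysis as complete-case among randomised participants, analysed as allocated, and include baseline glucose in the linear regression. Baseline glucose is already collected, so this needs only a text change.

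**Optional.** A finger-prick glucose at the three-month visit, with both visits in one mixed model and the six-month contrast primary, would let participants seen at month three but lost by month six contribute. It relies on a missing-at-random assumption and does nothing for those lost before month three. It would cost up to 216 extra test strips and a slightly longer visit; the point-of-care device is already budgeted. This is a design addition and is not needed to resolve the contradiction.

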**17. PRIMARY OUTCOME MEASURE**

**17.1 Glycaemic control**

The primary outcome measure is a change in glycaemic control from baseline to six months, measured as mean random blood glucose level. This will be assessed using a point-of care device which analyses a drop of fingertip capillary blood.

**18. SECONDARY OUTCOME MEASURES**

The secondary outcome measures will be assessed at three and six months namely;

- Knowledge on diabetes which will be obtained with the validated Michigan Diabetes Knowledge Test Questionnaire-2 (Fitzgerard et al., 2016).
- Medication adherence, using a pre-validated self-developed medication adherence questionnaire.
- Clinic attendance, using clinic registers.
- Quality of life, using the EQ-5D self-perceived quality of life questionnaire (EURO-QOL Group, 2009).
- Barriers to SMS intervention and the healthcare providers’ perception about SMS use using a self-designed questionnaire.
- Clinical (hypertension, overweight/obesity) and behavioural outcomes (Smoking, alcohol use, and physical activity) will be measured using the WHO modified STEPwise approach.
- Factors affecting adherence to diabetes therapy using a self-designed questionnaire

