**Social facilitation**

Influence

Support (health facilities, policies, support group, health education, SMS)

**Figure 1:** Integrated Behaviour Change model

10.2 **Application of the theory to the study**

Education and engagement in healthy lifestyle behaviour has been identified as key components in the improvement of health and management of chronic conditions. Glycaemic control and prevention of complications associated with diabetes requires diabetic individuals to engage in health promoting behaviours, and comply with therapeutic regimen. Based on the integrated theory of behaviour change, diabetic individuals will be assessed for their knowledge on diabetes, factors associated with adherence and diabetes control as well as their health beliefs related to diabetes. Participants’ glycaemic level, blood pressure, weight and behavioural characteristics will be assessed. Based on the findings of the initial assessment, participants will receive text messages tailored to their needs with the aim of increasing their knowledge, enhance their self-efficacy and outcome expectations in relation to their glycaemic level. Feedbacks from participants will also be expected as they will be encouraged to forward all queries or issues to the cell number that will be provided. At the end of the intervention, the measure of the expected outcome; self-management behaviours, improvement in lifestyle behaviours and ultimately clinical outcomes; weight, blood pressure, HbA1c, physical activity, smoking and alcohol use will be assessed.

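### No baseline is scheduled for medication adherence or EQ-5D, and the protocol's sections disagree on baseline knowledge, baseline blood pressure and the three-month collection

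*Protocol*

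**What the plan says.** The timing of assessments is spread over several sections of the protocol.

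- **Section 18** introduces its list with "The secondary outcome measures will be assessed at three and six months namely". The list holds the diabetes knowledge test, a self-developed medication-adherence questionnaire, the EQ-5D, clinical outcomes that include hypertension, and several other items.
- **Section 16** states "Data will be collected at baseline, and six months after the intervention". It then describes the baseline content: "Baseline data will include demographic characteristics including duration of diabetes, behavioural factors (smoking, physical inactivity, alcohol use"), followed by "anthropometric measurements (weight, height, waist and hip circumferences) and biochemical measurements (random blood sugar").
- **Section 10.2** describes an initial assessment whose results are used to tailor the messages: "diabetic individuals will be assessed for their knowledge on diabetes, factors associated with adherence and diabetes control". It adds "Participants’ glycaemic level, blood pressure, weight and behavioural characteristics will be assessed".
- **Section 17.1** defines the primary outcome as a change from baseline, so blood glucose has its starting value.
- **Section 24** has a row for data collection after three months. **Section 25** pays for data capture at baseline, three and six months, and for printing questionnaires for baseline and final collection. It does not say which instruments those questionnaires contain.
- **The aim** names adherence to anti-diabetic therapy beside glycaemic control. A specific objective covers medication adherence, and another reads "Determine the efficacy of the use of mobile phone SMS in improving diabetes knowledge among individuals living with diabetes".

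**The concern.** A protocol has to fix which instrument is given at which visit. An analysis plan cannot supply values that were never collected, and a pre-intervention score cannot be recovered once messages have started.

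A field team working from sections 16 and 18 would have no instruction to give the adherence questionnaire or the EQ-5D at baseline. They would also have no instruction to record knowledge or blood pressure then, although section 10.2 expects both. Medication adherence matters most here, because it is the behaviour through which the messages are meant to act and it is part of the overall aim. Without a starting value it could be compared between arms only at follow-up. The trial would have no within-person change, no check that the arms began alike on adherence, and no baseline adjustment to sharpen the estimate.

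**Working it through.** **Step 1: the schedules side by side.**

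| Measure | Baseline list, section 16 | Initial assessment, section 10.2 | Follow-up |
| --- | --- | --- | --- |
| Medication-adherence score | not named | not named (only factors associated with adherence) | 3 and 6 months |
| EQ-5D | not named | not named | 3 and 6 months |
| Diabetes knowledge | not named | named | 3 and 6 months |
| Blood pressure | not named | named | 3 and 6 months |
| Weight, and BMI from weight and height | named | weight named | 3 and 6 months |
| Smoking, alcohol, physical activity | named | behavioural characteristics | 3 and 6 months |
| Blood glucose (primary) | named | named | 6 months |

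Three things follow. Adherence level and EQ-5D have no scheduled baseline in any section. Knowledge and blood pressure have one in section 10.2 but not in section 16. The remaining measures shown have one. The factors in section 10.2 do not stand in for the adherence score, because section 18 lists the two as separate items with separate questionnaires.

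**Step 2: the three-month collection.** Section 16 gives baseline and six months. Sections 18 and 24 include three months. Section 25 is split: data capture covers three months, but the research-assistant line covers data collection at baseline and six months only.

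**Step 3: the plan's own figure.** The only power statement, in section 14, concerns HbA1c with a difference of 0.5, SD 1 and 90 per arm. It reproduces: 0.5/√(2/90) − 1.96 = 3.354 − 1.960 = 1.394, which gives a power of 91.8%, against a stated figure of over 90%. It does not bear on the secondary outcomes, so no figure in the protocol tests this point.

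**Step 4: what a baseline would be worth.** Let r be the correlation between baseline and six-month score. The protocol gives no value, so 0.3 to 0.7 is an assumption. In a randomised comparison, adjusting for baseline multiplies residual variance by 1 − r². The standard error is multiplied by √(1 − r²), and the equivalent sample-size factor is 1/(1 − r²).

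| Assumed r | Variance reduction r² | √(1 − r²) | 1/(1 − r²) |
| --- | --- | --- | --- |
| 0.3 | 9% | 0.954 | 1.10 |
| 0.5 | 25% | 0.866 | 1.33 |
| 0.7 | 49% | 0.714 | 1.96 |

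At r = 0.5 the confidence interval is about 13% narrower (1 − 0.866), as if a third more participants had been followed.

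**Step 5: dependence on the allocation.** Section 15 says both that individuals are randomised 1:1 and that separate districts serve the two arms. If individuals are randomised, a six-month comparison without baseline is unbiased by design. If districts are allocated, existing differences between districts mix with the message effect, and without baseline scores they could be neither seen nor partly adjusted for.

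**The case against.** The strongest reply is that silence is not exclusion. Section 18 does not say that its measures are taken at three and six months only. Its list also contains smoking, alcohol, physical activity and overweight, all of which section 16 does measure at baseline, so its sentence can be read as giving follow-up times. Section 16 says what the baseline will include, which need not be exhaustive. Section 10.2 mentions behavioural characteristics, and the theory figure in section 10 counts adherence to therapy among the self-management behaviours. Section 25 pays for baseline questionnaires. The sponsor may therefore intend to collect everything. This stands as a statement of possible intent. It does not amount to a schedule for the adherence score or the EQ-5D.

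A reader might go further and infer that the trial's objectives about improving or promoting outcomes lack a starting value, or that efficacy on adherence could not be shown at all. The protocol does not support either reading:

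- Glycaemia, weight, BMI and physical activity have a planned baseline, and section 10.2 plans one for knowledge and blood pressure.
- Quality of life appears in no specific objective.
- Under individual randomisation, the six-month difference between arms estimates the effect without any baseline.

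It is also fair to object that the district wording is a separate problem. Baseline scores would reduce confounding by district but would not cure it. Nor does the protocol show that baseline score is the strongest predictor of follow-up; the size of the gain rests on the assumed correlation.

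**Conclusion.** The point holds as a gap and an inconsistency in the assessment schedule for secondary outcomes. Medication adherence and EQ-5D have no scheduled baseline anywhere. Knowledge and blood pressure are planned in one section and omitted in another. The three-month collection is missing from section 16. The primary outcome is unaffected.

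If individuals are randomised, the consequence is lost precision, no change score and no balance check on these measures; validity is not at stake. The precision loss corresponds to forgoing a 9%, 25% or 49% cut in residual variance at assumed correlations of 0.3, 0.5 or 0.7. If districts are allocated, the comparison is also more exposed to bias. The change is worth making before enrolment, because it is cheap and the data cannot be obtained later.

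**What to change.** Reconcile sections 10.2, 16, 18 and 25 into a single schedule of assessments that does the following:

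1. Administers the medication-adherence questionnaire, EQ-5D, knowledge test and blood pressure at baseline and at three and six months. Items such as barriers to the messages, which need exposure to them, can stay at follow-up only.
2. Places the baseline measurements before allocation. This fits section 15, which already puts randomisation after baseline data collection.
3. Adds the three-month collection to section 16 and brings the staffing and printing lines of section 25 into agreement with it.
4. States that the effect on each of the four measures is the between-arm difference at six months adjusted for that measure's baseline value.

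The cost is a slightly longer interview at a baseline visit that already takes place. Baseline questionnaires and blood-pressure apparatus are already in the budget. The three-month collection is not new work, since section 18 already requires it, but the research-assistant line does not yet cover it.
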